#### Secondary outcome measures

The Perceived Competence Scale (PCS) measures the self-determination construct of patient perceived competence in their ability to increase their level of physical activity [17]. The PCS is a four item (Alpha reliability = 0.90) validated psychometric instrument to measure a person’s feelings of competence at carrying out a physical activity [55,56]. The PCS is administered to patients at baseline, post-intervention and follow-up as part of the post-visit survey’.

The Modified Health Care Climate Questionnaire (mHCCQ) [17] is a patient reported measure of the degree to which the clinician provides autonomy support, a construct derived from self-determination theory shown to be modifiable in health behavior interventions. The mHCCQ is a six item validated psychometric instrument that has been shown to be associated with behavior change for smoking cessation, weight loss and maintenance, and exercise. The mHCCQ measures patient perceptions of providers as autonomy supportive versus controlling and has been validated for use in primary-care offices (Alpha reliability is 0.92) [57]. The mHCCQ is administered at baseline, post-intervention and follow-up.

Clinicians’ perspectives on the intervention’s feasibility, sustainability, and learning objectives acquired, is assessed three ways: (1) via a survey administered at baseline and post-intervention, (2) via a process evaluation throughout the training period, and (3) via individual clinician post-intervention interviews. For the survey, we use a previously published survey from the Physical Activity for Life (PAL) study, which is a 20 item face-valid questionnaire to explore clinician impressions of the effectiveness of the intervention [13]. The survey contains items asking about clinician perspectives on feasibility, knowledge, and skills gained from the intervention. Ongoing process evaluation data are collected throughout the intervention’s training sessions in the form of field notes and audiorecorded feedback from clinicians during the training sessions. At the conclusion of the study, the principal investigator and research assistant conduct individual interviews to elicit clinician perspectives on feasibility of the intervention, relevance of training objectives, and suggestions for improvement.

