#### Exploratory outcome measures

Moderation variables consist of patient factors and visit factors. Patient factors are socio-demographic variables, body mass index, baseline health, [58,59] health literacy[60], co-morbidities, and length of relationship with their clinician. Visit factors consist of type of visit, measured categorically using the clinic schedules (e.g. routine follow-up, health care maintenance) and competing demands measured by the 1) number of topics discussed and 1) number of health behaviors discussed.

Mediation variables consist of patient perceived competence for physical activity (using the PCS), clinician autonomy support (using the mHCCQ) for physical activity, and patient recall of 5A using the Physical Activity Exit Interview (PAEI) [47]. The PAEI is a 12-item survey administered to patients after their visit asking them to recall specific content (Yes/No) to questions corresponding to each A for physical activity, such as “Did your doctor advise you to become more physically active?”, “Did your doctor discuss difficult situations you might encounter or problems you might have in trying to become more physically active?”, and “Did your doctor state that he/she is planning to discuss your physical activity on a future visit?”

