**Figure 2 F2:**
[figure not shown]
Mediators and moderators to be assessed in exploratory analyses.

The clinicians will be included as a random effect, and intervention group, time, and baseline 5A scores will be included as fixed effects. The interaction between treatment and time will be used to assess whether the treatment effect (of the intervention) changes with time.

Secondary analyses include similar modeling approaches for the secondary outcome variables: autonomy support (mHCCQ), patient perceived competence (PCS) and clinician feasibility (PAL). Clinician feasibility will also be qualitatively analyzed using the process evaluation data and individual clinician exit interviews. The secondary hypotheses (H2-H4) are as follows:

H 2: The intervention will increase clinician use of the PCC construct autonomy supportiveness as assessed by the mHCCQ in the post-intervention period (immediately post and at one year) compared to baseline.

H 3: The intervention will increase patient perceived competence (accessed via the PCS) for adopting physical activity.

H 4: Specific patient recall of the Assist and Arrange will be associated with the greatest patient perceived competence to adopt physical activity compared to recall of Ask, Advise, or Assess.

Hypotheses 2–4 will be tested by measuring the changes in the mHCCQ, PCS, and PAEI scores, respectively, for patients seen by clinicians in Group 1 in the post-intervention period (immediately post and at one year) compared to baseline. compared to the Group 2 baseline and Group 1 baseline. We will also compare change in the 5A scores for Group 2 post-intervention compared to Groups 1 and 2 baseline scores.

Exploratory analyses will use a similar approach to that used for the primary analysis, to examine whether the primary outcome (5A score) was mediated by patient perceived competence (PCS score), clinician autonomy supportiveness (mHCCQ score), or patient recall of the 5As (PAEI score). Additional exploratory analyses will examine the role of selected factors that may moderate the relationship between the intervention and the 5A score: continuity of care, patient socio-demographic variables, patient BMI, baseline health, health behaviors, health literacy, and competing demands. Regression-based statistical models will be constructed and examined. The Diagram below shows the inter-relationship of the mediating and moderating factors to be explored in this analysis.

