### Design limitations and other considerations

Maximizing clinician adherence, consistency and fidelity to any intervention in a clinical setting is challenging. Steps to address these issues are to give positive feedback, regular updates, encouragement and incentives for the clinicians, nursing staff, and organization. It is possible that improvement after intervention will be minimal and difficult to sustain given the competing needs and challenges inherent in working with underserved patient populations. Thirdly, cross-contamination, spillover, and/or Hawthorne effects are concerns in this study; we will assess these issues in our analysis taking advantage of the two group design feature and directly audio-recorded, objective data source as well as post-study clinician interviews asking them to estimate the extent to which they may have been biased by the presence of the recorder. Finally, this study is unable to follow a cohort of patients pre- and post- intervention, though it is possible to look at aggregate baseline- and post-intervention patient-level factors that may affect use of the 5As. Given the relatively small scale of this project, this limitation is a recognized trade-off for practical and logistical considerations. The first priority for this project is to look at clinician implementation issues. Patient outcomes are secondary and exploratory in this study but will be key in future work.

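### H2 and H3 compare different patients before and after training, and the stated model has no patient-level terms to absorb a shift in patient mix

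*Protocol article*

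**What the plan says.** All places are in the protocol article.

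- **Statistical analyses**, on H2 to H4: the hypotheses are tested "by measuring the changes in the mHCCQ, PCS, and PAEI scores, respectively, for patients seen by clinicians in Group 1", after training versus before, "compared to the Group 2 baseline and Group 1 baseline".
- **Secondary outcome measures**: "The PCS is administered to patients at baseline, post-intervention and follow-up as part of the post-visit survey". For autonomy support, "The mHCCQ is administered at baseline, post-intervention and follow-up". Both are patient-reported.
- **Design limitations and other considerations**: "this study is unable to follow a cohort of patients pre- and post- intervention". The section calls this a practical trade-off. It adds that aggregate patient factors could be examined, but only in relation to use of the 5As.
- **Statistical analyses**, on the model: clinician is a random effect, and "intervention group, time, and baseline 5A scores will be included as fixed effects", with a treatment-by-time interaction. The secondary outcomes get a similar model.
- **Exploratory outcome measures**: patient factors (socio-demographics, BMI, baseline health, health literacy, co-morbidity, length of relationship) and visit factors are collected. On the latter, "Visit factors consist of type of visit, measured categorically using the clinic schedules". Statistical analyses gives such factors one role, as exploratory moderators of the 5A score.
- **Procedure for randomization**: clinicians and research staff know the group assignment.

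**The concern.** The word *changes*, applied to patients' scores, suggests that each patient has a value before and a value after. The plan provides for no such pairs: the scales are completed after a recorded visit by whoever was recruited at that time point. A before-after difference in mean PCS or mHCCQ therefore mixes two things, the effect of training and any difference between the patients sampled early and those sampled late.

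The stated model has nothing to separate the two, although the information is collected. If the later patients were, for example, younger or had fewer co-morbidities, a higher mean PCS could be credited to the training. For mHCCQ and PCS the article gives the patient factors no role at all, not even an exploratory one.

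**Working it through.** **1. The plan's one power figure does not bear on H2 and H3.** Sample size and power gives SD 1.06 and a detectable difference of 0.54 at 80% power (two-sided 0.05), for the 5A score. The formula is (1.96 + 0.84) × SD × √(1/n₁ + 1/n₂).
- All 300 visits, 8 × 20 = 160 versus 7 × 20 = 140: 2.80 × 1.06 × √(1/160 + 1/140) = 0.34.
- Eight visits per clinician, 64 versus 56: 2.80 × 1.06 × √(1/64 + 1/56) = 0.54.

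The 0.54 thus matches about eight visits per clinician, not 20, if clustering is ignored. Nothing below depends on it. No SD or target difference is given for mHCCQ or PCS, so the rest is in SD units.

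**2. What is estimable.** The scales are part of a post-visit survey, and no cohort is followed. The quantity is the mean among patients sampled after training minus the mean among patients sampled before, for the same clinicians.

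**3. Can the mix differ systematically?** The document gives three reasons.
- Research staff screen clinic schedules and consent patients while knowing the allocation (Participant eligibility; Patient participant recruitment and enrollment; Procedure for randomization).
- Baseline recruitment can be extended past 10 visits per clinician if physical activity has not come up, and continues until there is enough baseline information on such discussions (Recruitment of clinician participants; Patient participant recruitment and enrollment). After training the number is set at 15 over two points. The samples may therefore be drawn by different rules.
- The comparator named for H2 to H4 is the two baselines. Group 2's second untrained assessment, which Group 2 (wait-list) places alongside Group 1's post-intervention assessment, is not named there. A calendar-time shift is not cancelled in the comparison as worded.

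**4. H1 is different.** The primary analysis compares scores between and within groups and has a group-by-time term. A shift common to both groups cancels in that contrast; only a differential shift remains.

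**5. Illustration for Group 1, baseline versus one later point.** Inputs: 8 clinicians, 10 visits at baseline (80 patients) and 7.5 later (60 patients); clustering ignored.
- Standard error: √(1/80 + 1/60) = 0.171 SD. Detectable difference: 2.80 × 0.171 = 0.48 SD.
- If surveys were lost at the 20% assumed for recordings (64 versus 48): standard error 0.191 SD, detectable difference 0.54 SD (0.535).
- Chance imbalance in a covariate, 95% limit: 1.96 × 0.171 = 0.34 SD, or 1.96 × 0.191 = 0.37 SD after loss. This is noise that the standard error already reflects. Adjustment would reduce it, but it is not bias.
- Bias from a systematic shift = shift in the covariate × its standardised effect on the score. Assumed shifts of 0.2 to 0.5 SD and effects of 0.2 to 0.5 give 0.2 × 0.2 = 0.04 SD up to 0.5 × 0.5 = 0.25 SD. That is 0.04/0.171 = 0.23 to 0.25/0.171 = 1.46 standard errors.
- Precision gained if the covariates explain 10% to 30% of the variance (assumption): 0.48 × √(1 − 0.1) = 0.45 down to 0.48 × √(1 − 0.3) = 0.40 SD.

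**The case against.** **The missing cohort is disclosed, and the wording can be read correctly.** The abstract speaks of repeated measures from each clinician and of aggregate group measures, and the primary analysis compares means. Clinicians are the randomised and repeatedly measured unit. A mixed model with a clinician random effect can validly analyse successive patient samples. This stands. A reader might infer that H2 and H3 cannot be tested at all; the document does not support that. The wording part is a clarification of the estimand and changes no estimate.

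**Covariate lists usually sit in an analysis plan that is not shown.** This stands in part: adjustment is not ruled out. But the article does list the fixed effects, and it assigns the patient and visit factors to a different purpose.

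**Adjusting for everything collected could do harm.** This stands. A reader might infer that visit type, BMI and SF-12 belong in the main models. The document does not show them to be unaffected by training: the SF-12 is taken after the visit, training encourages clinicians to arrange follow-up, and follow-up is an eligible visit type. A patient seen late may also have been counselled earlier.

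**The secondary outcomes may also get a group-by-time contrast**, since they use a similar model. If that contrast were the test, only a differential shift would matter. The sentence on H2 to H4 nevertheless names baselines as the comparator.

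**A large share of the 0.54 target might seem explainable by visit mix.** For instance, a 30-point shift in visit type times a score gap of 1.0 gives 0.30, or 56% of 0.54. Both inputs are invented, a gap of 1.0 exceeds the whole pilot mean of 0.74, the outcome is the 5A score rather than mHCCQ or PCS, and 0.54 is a between-group difference. That calculation does not size this concern.

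**Conclusion.** The point holds as a modest one. H2 and H3 rest on differences between separate patient samples, and the model as stated does nothing about patient mix, although suitable variables are collected. The risk applies to the H2 and H3 comparisons against baseline; for H1 it is limited to shifts that differ between the groups.

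The size is unknown. The 0.04 to 0.25 SD range shows only how the bias scales with assumed inputs, and no shift in mix has been shown to occur. The conclusion rests on reading the listed fixed effects as the intended model and the baselines as the intended comparator. The consequence is tempered by the trial being a pilot with patient outcomes declared secondary and exploratory, but the correction is cheap.

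**What to change.** 1. Word H2, H3 and the matching secondary outcomes as differences in mean mHCCQ and PCS between the patient samples seen before and after training, within clinician, rather than as change in patients.
2. Add to the mHCCQ and PCS models a short prespecified set of collected patient characteristics that training cannot plausibly change, such as age, gender, education and co-morbidity. Use the same set in a supporting adjusted analysis of the 5A score.
3. Use visit type, BMI and SF-12 only in a sensitivity analysis, and say why.
4. Report the unadjusted result alongside.

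The cost is some rewording and a few visit-level terms, against about 300 analysable visits. No new data are needed. The downside is the loss of some visits with a missing covariate.

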### Group 2 (wait-list)

The clinician baseline assessment for Group 2 is identical to that for Group 1. The Group 2 assessment occurs at 0–3 months (concomitant with the Group 1 clinician baseline) and again at 9–12 months (concomitant with the Group 1 post-intervention assessment.)

Group 2’s clinician training intervention occurs in the same manner as described in the section, Description of Intervention (section 2.11) for Group 1. Standardization of both Group 1 and Group 2’s training intervention sessions is assessed by audio-recording all sessions and ensuring that the key objectives of each session are met using a pre-developed checklist and via rating by a trained research staff member not involved in delivering the intervention.

Group 2’s Post-Intervention Assessment occurs immediately post-intervention and at six months post-intervention in the same manner as described previously for Group 1 (section Post-Intervention Clinician Assessment). As with Group 1, Group 2 clinicians also complete a survey asking about the feasibility of the intervention and individual exit interviews.

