### Statistical analyses

The primary outcome measure will be the 5A score as described in (section Primary outcome measure: 5As score). The primary analysis will use a mixed effect model to compare mean 5As scores between and within each group for each of the three time points: baseline, immediately post-intervention, and follow-up. The primary hypothesis (H1) is: Clinicians who complete the communication intervention will increase their use of all 5As for all visits in which the topic of physical activity is raised as judged by audio-recordings of office visits in the post-intervention period (immediately post and at one year) compared to baseline. Figure 2 shows the analysis plan for hypothesis testing and exploratory outcomes.

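### The sentence defining the H2 and H3 tests leaves out Group 2's post-training PCS and mHCCQ surveys and conflicts with the two-group modelling planned for the same outcomes

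*Protocol article*

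**What the plan says.** Three statements in the Protocol article's Statistical analyses section bear on which surveys test H2 and H3.

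- The sentence assigning data to Hypotheses 2–4 takes the change in mHCCQ, PCS and PAEI "for patients seen by clinicians in Group 1 in the post-intervention period (immediately post and at one year) compared to baseline". A detached fragment then adds the comparator: "compared to the Group 2 baseline and Group 1 baseline".
- The next sentence is the only explicit use of Group 2's post-training data: "We will also compare change in the 5A scores for Group 2 post-intervention compared to Groups 1 and 2 baseline scores". It names neither mHCCQ nor PCS.
- Earlier in the section: "Secondary analyses include similar modeling approaches for the secondary outcome variables", with mHCCQ and PCS listed among them. The model they are to resemble is the primary one, which will "compare mean 5As scores between and within each group for each of the three time points: baseline, immediately post-intervention, and follow-up", with group, time and their interaction.

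The surveys will exist. In the section Group 2 (wait-list), "Group 2’s Post-Intervention Assessment occurs immediately post-intervention and at six months post-intervention in the same manner as described previously for Group 1". Under Secondary outcome measures, "The PCS is administered to patients at baseline, post-intervention and follow-up as part of the post-visit survey", and the mHCCQ follows the same schedule.

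**The concern.** One rule limits the post-training evidence for H2 and H3 to Group 1. The other implies a model in which both groups appear at every time point. These use different samples and can give different estimates. Two analysts could each follow the section faithfully and report different results, and the choice could be made after the data are seen.

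Under the first rule, patient-reported data that the study pays for and collects are not used for the hypotheses they were collected to test. Group 2 trains later, so it also offers a second look at the change in patient outcomes in other clinicians at another calendar time. The article gives no reason for setting that aside.

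**Working it through.** **1. The plan's own count.** Sample size and power gives at most 15 clinicians (8 in Group 1, 7 in Group 2) with 25 visits each: 15 × 25 = 375, and 375 × 0.80 = 300. Both figures reproduce. The 20% loss is attributed to recordings, so planned visits are used below.

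**2. Share of post-training surveys omitted.** Recruitment of clinician participants gives 10 baseline and 15 post-training visits per clinician.
- Group 1: 8 × 15 = 120. Group 2: 7 × 15 = 105. Share: 105/225 = 46.7%.
- Sample size and power also gives Group 2 four time points within the 25 visits. Spread evenly, there are 6.25 per point, so 12.5 after training: 7 × 12.5 = 87.5, and 87.5/207.5 = 42%.
- If each of two pre-training assessments takes 10, then 5 remain: 7 × 5 = 35, and 35/155 = 23%.

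**3. Precision with no calendar-time change.** Set the total variance to 1 and the ICC to ρ. The documents give no ICC for PCS or mHCCQ, so 0.01 to 0.20 is assumed. Worked case: ρ = 0.05, with 10 pre-training and 15 post-training visits per clinician.
- All data, both groups: SE = √[(1−ρ)(1/10 + 1/15)/15] = √(0.95 × 0.16667/15) = 0.103.
- Group 1 post-training against both baselines combines two differences optimally. Against Group 1's own baseline: v1 = 0.95 × 0.16667/8 = 0.01979. Against Group 2's baseline: v2 = (0.05 + 0.95/15)/8 + (0.05 + 0.95/10)/7 = 0.01417 + 0.02071 = 0.03488. Their covariance: c = 0.01417 − 0.05/8 = 0.00792. Variance = (v1·v2 − c²)/(v1 + v2 − 2c) = 0.000628/0.03884 = 0.01616, so SE = 0.127.
- Ratio: 0.127/0.103 = 1.24.

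The same generalised least squares calculation was run with Group 2's visits over four points, both of its pre-training assessments kept, ρ from 0.01 to 0.20, and a clinician-by-period variance of 0 to 0.05. Ratio of SE without Group 2's post-training surveys to SE with them:

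| Group 2 visits (pre, pre, post, post) | Ratio |
|---|---|
| 6.25 at each point | 1.18–1.34 |
| 5, 5, 7.5, 7.5 | 1.18–1.33 |
| 10, 10, 2.5, 2.5 | 1.10–1.25 |

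**4. Precision with calendar period in the model.** Four periods are assumed: both baselines; Group 1 immediate post with Group 2's second pre-training assessment; Group 1 follow-up with Group 2 immediate post; Group 2 follow-up. The ratios for the same three rows become 1.00–1.08, 1.00–1.09 and 1.00–1.04. Group 2's last assessment has no concurrent Group 1 data, so it adds almost nothing.

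Adjusting for period has its own price. At ρ = 0.05 with the even split, the SE with all data rises from 0.10 to 0.21 SD. If Group 2's second pre-training assessment is left out, every survey in the first period is untrained and every later one is trained, so training and period cannot be separated at all.

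**The case against.** The case against is substantial, and much of it stands.

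- **A reader might infer that Group 2's post-training surveys never enter any secondary test.** The documents do not support that. The sentence on similar modelling names mHCCQ and PCS and points to a two-group model, and the restricting sentence is visibly garbled. What is established is an unreconciled conflict, not a clear exclusion.
- **A reader might infer that H2 and H3 rest on 8 of 15 clinicians.** Only the post-training side does. Group 2's baseline is named as a comparator, so all 15 contribute.
- **A reader might quote a 37% wider interval**, since √(15/8) = 1.37. That is the ratio for Group 1 against its own baseline alone, which is not the comparator the section states.
- **The precision loss largely disappears once secular change is allowed for.** This is correct, as step 4 shows. Pooling all before-after data without a period term would also be open to the Hawthorne and spillover effects that the article itself lists under Design limitations.
- **Not relying on wait-list data after crossover is a defensible choice, and patient outcomes are secondary in a pilot.** Also fair. But the article does not state that choice, and it uses Group 2's post-training data for the 5A score.

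**Conclusion.** The point holds as a conflict between two statements in one section. The one that defines the H2 and H3 tests leaves out Group 2's post-training surveys.

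The omitted share is 47% with 15 post-training visits per clinician, and 23% to 42% under the two alternative four-point splits tried. The cost in standard error is about 10% to 34% if there is no calendar-time change, and about 0% to 9% with calendar period modelled. These figures rest on assumed ICCs, an assumed visit split and an assumed alignment of the two groups' assessments.

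The gain in precision is therefore modest. The firmer reason to act is that the article should fix one analysis set for H2 and H3. The primary 5A analysis is not affected.

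**What to change.** Replace the Group 1 sentence by:

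> H2 and H3 are tested in one mixed model using the surveys of patients of all clinicians in both groups at all assessments, with training status (pre/post) and calendar period as fixed effects and clinician as random effect; group-specific estimates are also reported.

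The period term should not be dropped, because without it the test is an uncontrolled before-after comparison. The model needs PCS and mHCCQ at Group 2's second pre-training assessment. The article should say that they are collected there and fix when it occurs: Group 2 (wait-list) gives 9–12 months, while Assessing cross-contamination gives months 12–15.

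The cost is a few words in the analysis section, with no added visits or data. The H2 and H3 result waits for Group 2's final assessment, which the study already collects. With the period term the interval will be wider than that of a simple before-after comparison, and the report should say so.
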